## Abstract

**Background:**

Long COVID is a collection of symptoms that develop during or following a confirmed or suspected case of COVID-19, which continue for more than 12 weeks. Despite the negative impact of long COVID on people’s lives and functioning, there is no validated treatment or even rehabilitation guidance. What has been recommended thus far is the adoption of holistic management approaches. The Optimal Health Program (OHP) is a brief 5-session, plus booster, psychosocial program designed to support mental and physical well-being that has been used effectively for a range of chronic conditions.

**Objective:**

This study examines the feasibility and acceptability of employing an especially customized version of OHP (long COVID OHP [LC-OHP]) to improve psychological and physical health of people with long COVID.

**Methods:**

This is a feasibility randomized controlled trial that will be running from November 2021 to February 2023. Eligible participants aged 18 years or older who are experiencing symptoms of long COVID will be identified through their secondary practitioners with recruitment to be undertaken by the research team. A total of 60 participants will be randomized into a control (usual care) or an intervention (LC-OHP) group. Outcomes will be feasibility and acceptability of the program (primary); and efficacy of the LC-OHP in improving anxiety, depression, fatigue, self-efficacy, and quality of life (secondary). Up to 20 participants will be interviewed at the end of the trial to explore their experience with the program. Quantitative data will be analyzed using SPSS, and differences between groups will be compared using inferential tests where appropriate. Qualitative data will be transcribed and thematically analyzed to identify common emerging themes.

**Results:**

This is an ongoing study, which began in November 2021.

**Conclusions:**

Long COVID has a significant impact on an individual’s mental and physical functioning. The LC-OHP has a potential to provide people living with long COVID with additional support and to improve self-efficacy. The findings of this study would identify the feasibility of delivering this program to this population and will provide an indication for the program’s effectiveness.

**Trial Registration:**

ISRCTN Registry ISRCTN38746119; https://www.isrctn.com/ISRCTN38746119

**International Registered Report Identifier (IRRID):**

DERR1-10.2196/36673

## Introduction

### Background

COVID-19, as named by the World Health Organization, is a novel virus that emerged in Wuhan, China in December 2019 and spread rapidly across the whole world resulting in a global pandemic [1-3]. From the start of the pandemic to date, there are more than 246 million confirmed cases of COVID-19 across the world, of which there is around a 90% recovery rate, although more than 4 million people have died [4,5]. Several measures have been implemented to limit its spread, including avoidance of public contact, maintaining social distance, case detection, contact tracing, the use of personal protective equipment such as face masks, and encouraging hand hygiene practices [6,7].

COVID-19 infection is generally believed to be a short-term illness, from which people recover in about 2 weeks [8]. Figures indicate that around 80% of affected people develop a mild to moderate disease, and 5% of those with severe disease develop a critical illness [9]. Recovery usually takes 7-10 days following the onset of the mild infection and 3-6 weeks in the severe or critical illness [10]. In some people, certain symptoms persist in the postacute phase [11,12]. This condition has been given several labels, including long COVID, post-COVID syndrome, long haulers, postacute COVID-19, and persistent COVID-19 symptoms [11,13,14]. Whatever the term, each describes an illness in which symptoms persist longer than expected, or where there are lasting effects of the infection [2]. In the absence of an alternative explanation, long COVID encompasses ongoing symptoms of COVID-19 lasting 12 weeks or more [2,12,15-18].

COVID-19 is a new virus; as such, there are many unknown aspects surrounding its trajectory, including who is susceptible to long COVID and why recovery is prolonged for some people. While it is not yet possible to identify who may develop long COVID, there appears to be several risk factors including female sex, increased age [15], presence of more than 5 symptoms in the acute phase [19], associated comorbidities, and extended duration of acute illness [14,19-23].

A recent systematic review, which included 25 studies with 5440 participants, reported the frequency of long COVID to be up to 80% of the included population [17]. Another study showed that some symptoms persisted 3 months post hospital discharge [24]. Moreover, it seems that anyone can develop long COVID, including young people with no preexisting health conditions [18,25]. In the United Kingdom, the Office of the National Statistics and the UK COVID-19 symptom study app show that 1 in 5 people have COVID-19 symptoms that persist after 5 weeks, and 1 in 10 have symptoms that persist longer than 12 weeks [8,26]. To date, more than 8 million cases of COVID-19 have been confirmed in the United Kingdom [5], with more than 2 million people reporting they may have had long COVID [27], but the number is expected to increase as the virus is still active in the community.

Symptoms of long COVID vary between individuals. It seems to affect multiple organ systems in the body, and patients can present with single, multiple, constant, transient, or fluctuating symptoms [12,28], in a continuous or a relapsing and remitting course. According to a recent meta-analysis, the five most commonly reported symptoms are fatigue (58%), headache (44%), attention disorder (27%), hair loss (25%), and dyspnea (24%) [13]. Fatigue was found to be independent of the severity of the initial viral infection and to develop irrespective of a preceding hospitalization [29]. Long COVID represents a challenge for both the patient and the health care provider as it can be difficult to diagnose with certainty and may influence the doctor-patient relationship and trust [30]. Other reported manifestations of long COVID include cough, joint pain, chest pain, and low-grade fever [8,31,32].

Encountered neuropsychiatric symptoms include anosmia, brain fog, and neuropathy [33,34]. COVID-19 doubles the risk of developing a psychiatric disorder [35]. Anxiety, depression, or posttraumatic stress was manifest in 56% of patients with long COVID [36]. Social isolation, decreased physical activity, changed habits, as well as social and economic insecurity that are associated with the pandemic may contribute to developing the physical and psychological symptoms of long COVID [17,37].

The lack of sufficient information on this condition, along with variability in presenting symptoms and disease course between individuals, adds further challenges to identifying the best practice for its management and control. To date, no clear treatment regime is available to mitigate long COVID, and treatments given are dependent on presenting complaints. Minor complaints such as fever or cough can be treated symptomatically with paracetamol, cough suppressants, or antibiotics if a secondary bacterial infection is suspected [14]. Patients are advised to follow the “three P’s principle,” which is as follows: “Pace” to conserve energy when doing daily activities; “Plan” activities across the week; and “Prioritize” necessary tasks to get a mixture of activities that will boost mental health every day [38].

The complexity and diversity of symptoms of long COVID demand the use of individualized care plans [39]. The focus should not be on providing symptom by symptom management, but rather on delivering holistic, integrated care, bringing together patients and health care practitioners from across all specialties to achieve a common goal and meet the long-term needs of this population [11,40,41]. In the United Kingdom, a 5-point plan was recently set by the National Health Service (NHS) in response to the challenge of long COVID [18]. This included the launch of several clinics to tackle the persistent symptoms of COVID-19 [18,31], the creation of “Your COVID Recovery” website that provides reliable and up-to-date information and support [42], and the investment of millions of pounds in research to gain better understanding of this condition. Additionally, guidance was published to support clinicians in providing care to patients with long COVID [12,43].

Attention to mental health is also important as restrictions associated with the pandemic limited the provision of mental health services [44-46]. Although at the beginning, accessing mental health services decreased [47], numbers slowly started to increase and are now at a record high [47-49]. In 2020, the Office of the National Statistics reported that well-being levels were at their lowest since data collection started in 2011 [50], and that this has been greatly influenced by the pandemic. There has been a significantly increased demand on local beds [51], and the need for new or additional mental health support is expected to increase over the next 3 to 5 years [52,53] to a level that is 2 to 3 times that of the current NHS capacity [54]. There is an obvious and critical need to provide alternative supports; integrated, psychological, and mental health support that is readily accessible to all patients.

Long COVID highlights the need for a specialized intervention to manage complex comorbidities. In this context, the Optimal Health Program (OHP) is a form of psychosocial intervention [55] that provides clinicians with a consistent approach to support patient self-management. This approach challenges traditional methods of health care by encouraging patients to be actively involved in their own management [56] as this is anticipated to be more effective than using passive approaches [57]. The OHP has been shown to be beneficial for people with other chronic conditions such as diabetes [58], stroke [59], and chronic kidney disease [60]. However, no research has yet evaluated its use in patients with long COVID. The Long COVID OHP (LC-OHP) program aligns with the NHS and the National Institute for Health and Care Excellence (NICE) guidelines for managing and supporting long COVID by promoting shared decision-making and by delivering care that meets the individual needs and preferences of patients. Additionally, it provides care to patients in an easy-to-understand way and signposts them to useful resources for more support, as recommended by current guidelines [61].

Through the application of the tailored LC-OHP sessions alongside those living with long COVID, this study will examine if this program is feasible and acceptable in improving individual’s psychological and physical health.

### Aim and Objectives

This study aims to examine the feasibility and acceptability of the LC-OHP and evaluate any impact on quality of life, depression and anxiety, fatigue, and self-efficacy in patients with long COVID, compared to usual care. The study objectives are as follows:

#### Primary Objectives

The primary objectives are to determine the feasibility of conducting a 5-week psychosocial intervention in patients with long COVID by identifying the following outcome measures: (1) acceptability, recruitment, and retention rates; (2) participant’s satisfaction with the intervention; and (3) appropriateness of secondary outcome measures.

#### Secondary Objectives

The secondary objectives are to evaluate the preliminary efficacy of the LC-OHP in improving quality of life, depression and anxiety, fatigue, and self-efficacy in people with long COVID, compared to usual care.

## Methods

This protocol is reported using the SPIRIT (Standard Protocol Items: Recommendations for Interventional Trials) reporting guidelines [62].

### Research Design and Setting

This research is a feasibility randomized controlled trial to be conducted from November 2021 to February 2023 by investigators from the University of Suffolk. Potential participants will be identified from a long COVID clinic located within a hospital setting.

### Participants

#### Inclusion Criteria

Patients meeting the following criteria will be included in the study: (1) adults ≥18 years old; (2) COVID-19 infection confirmed through polymerase chain reaction testing or clinical diagnosis from a general practitioner; (3) experiencing post–COVID-19 syndrome (as defined by NICE 2020) 12 weeks or more following onset of symptoms or confirmed through testing; (4) able to participate in a telephone interview in English language (or with accommodated adjustments); and (5) able to consent to participate in the study.

#### Exclusion Criteria

Patients will be excluded if they meet any of the following criteria: (1) children and young adults (17 years and under); (2) unable to consent to participate in study; and (3) unable to participate in a telephone interview in English language.

#### Sample Size

A total of 60 patients will be recruited to the trial, with 30 randomized to the intervention or control group. The sample size has been determined according to the recommendations that at least 30-35 patients be included per group for pilot and feasibility studies [63-66].

### Study Procedures

#### Consent and Recruitment

Eligible participants who are referred to the long COVID clinic will be identified and approached by the clinical team on their initial visit to the clinic that is located at a hospital setting. As part of their initial assessment, the team will provide a brochure that outlines the trial and details of the research team to contact if they would like to take part. After expressing interest, the research team will provide eligible participants with the trial’s participant information leaflet and a consent form with a prepaid envelope. The research team will then contact the participants after 5 working days of sending the documents to answer any queries and to remind them to send their signed consent form.

#### Baseline Data Collection

Following the receipt of signed consent forms, the research team will contact participants to agree on the logistics of completing the questionnaires. Questionnaires will be sent to participants by email or post. With the baseline questionnaire, participants will also complete a short questionnaire to collect demographic data (ie, age, gender, ethnicity, and education). Participants will also have the option to complete the questionnaires on their own (ie, self-completion) or by telephone supported by a member of the research team. Responses to questionnaires will be recorded on a secure electronic database. Two reminders will be sent to nonrespondents. If no response is received, participants will be removed from the study. Table 1 provides a summary of the questionnaires to be completed by participants in the study at baseline, 3 months, and 6 months post randomization.

**Table 1 table1:** Overview of questionnaires.

Questionnaire	Outcome	Details
PHQ-9^a^	Depression	A 9-item validated questionnaire with 4 response options: “not at all” (scored as 0) to “nearly every day” (scored as 3). PHQ-9 total scores range from 0 to 27, with scores of ≥5, ≥10, and ≥15, representing mild, moderate, and severe levels of depression severity [67]. The questionnaire can be administered over the phone.
GAD-7^b^	Anxiety	A 7-item, easy-to-use, self-administered questionnaire, answered using a 4-point scale (from 0 to 3). It is used as a screening tool and severity measure for generalized anxiety disorder [68,69].
GSE^c^	Self-efficacy	A 10-item questionnaire rated using a 4-point Likert scale (“not at all true” to “exactly true”). The questionnaire tests the individual’s self-efficacy (ie, his or her ability to organize and execute certain behaviors that are necessary in order to produce given attainments). Higher scores are indicative of higher self-efficacy. The questionnaire is valid and reliable with high internal consistency [70].
EQ-5D-5L^d^	Quality of life	A validated 5-item questionnaire scored on 5-item answers. It provides a generic measure on the following health dimensions: mobility, self-care, usual activities, pain or discomfort, and anxiety or depression [71]. The questionnaire also includes a visual analogue scale with scores ranging from 0 to 100 to reflect current health status [72].
FAS^e^	Fatigue	A validated 10-item questionnaire that is answered using a 5-point answer scale: “never” (scored as 1) to “always” (scored as 5) [73,74].

^a^PHQ: Patient Health Questionnaire.

^b^GAD-7: Generalized Anxiety Disorder.

^c^GSE: General Self-Efficacy.

^d^EQ-5D-5L: European Quality of Life 5 dimensions, 5 levels.

^e^FAS: Fatigue Assessment Scale.

### Randomization, Allocation, and Blinding

Participants will be randomized following the receipt of baseline data to either intervention or control group using a computer-generated block randomization. To avoid bias, an independent person will carry out participant randomization. Due to the nature and length of the intervention, it is not possible to blind either the research team or the participant to the treatment allocation.

Participants allocated to the control group will receive usual care provided to patients with long COVID, depending on presenting complaints and assessments. The intervention group will receive the LC-OHP plus usual care.

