Sessions will be delivered weekly with a booster session to be held 3 months after the last session. The booster session will target reviewing health plans and reflecting on achievements made toward health-related goals. Sessions will be held either in a 1:1 encounter with the facilitator, or in groups, or using a mixture of both, depending on participants’ preferences. Each 1:1 session will last up to one hour, with breaks provided upon participant’s request, and if necessary, the session can be completed at another time. Group sessions will last up to 90 min, and breaks will be provided upon request. Sessions will be held online (using a convenient platform) or by telephone (to those who do not have access to online facilities). Sessions will be audio-recorded to be checked by another member of the research team to confirm fidelity of program delivery. Participants can contact facilitators between the sessions if they have any questions or wish to change the time for the next session.

Facilitators have received prior training in delivering the program during a 2-day workshop delivered by one of the investigators ([name]) who developed the OHP program. Regular supervision will also be provided to facilitators to ensure fidelity with program delivery and to discuss any concerns. Additionally, a fidelity checklist will be completed by the facilitator after the end of each session to ensure all core components of each session have been covered. The checklist will also be reviewed by another member of the research team to ensure fidelity.

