### Qualitative Interviews

After the end of the trial, participants allocated to the intervention group will be invited to participate in a semistructured telephone interview conducted by an independent researcher (not the OHP facilitator). The interview will target exploring participants’ experience with the LC-OHP, identify their views on the program, and share any suggestions for improving the program for the future. Interviews will be audio-recorded and will be conducted at a time convenient to the participant. Interview duration will last up to 30 min (a max of 40 min if a participant requests more time) and will be guided by a topic guide developed by the research team. Participants will be interviewed until data saturation is reached. Textbox 1 shows a summary of the interview topic guide list.

Summary of the interview topic guide list.

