### Data Analysis

Quantitative data analysis will be performed using SPSS (IBM Corp). Descriptive data will be presented using means, interquartile range, and percentages. Differences between the groups will be compared using appropriate inferential tests.

For the qualitative data, interviews will be recorded (with informed consent), transcribed verbatim, coded, and thematically analyzed (using an inductive thematic analysis approach) to identify common emerging themes [81]. Transcripts will be continuously revisited, and the accuracy will be verified by listening to the recordings and comparing them with the transcripts. Coding of data will be conducted using NVivo (QSR International), and codes will be checked by another member of the research team to ensure appropriate and consistent coding process. Any disagreements will be resolved by consensus, and by referring to the transcripts and original recordings.

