### Strengths and Limitations

The study has some limitations. Due to the nature of the intervention, participants and researchers will not be blinded to group allocation; however, to avoid researcher-induced bias, randomization and interviews will be conducted independently.

To the authors’ best knowledge, this is the first study to examine an individualized holistic psychosocial program designed to address the needs of adults experiencing long COVID. The study is anticipated to provide evidence for the feasibility and acceptability of the used intervention in improving health outcomes for people experiencing long COVID. This feasibility trial uses a mixed methods design to assess procedural and methodological data in preparation for a fully powered large-scale trial.

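### The protocol declares the whole research team impossible to blind, but the reason it gives does not reach whoever cleans, scores and compares the questionnaire data

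*Protocol article*

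**What the plan says.** Under Randomization, Allocation, and Blinding, the reason for not blinding is introduced with "Due to the nature and length of the intervention", and the conclusion is that "it is not possible to blind either the research team or the participant to the treatment allocation". No exception is made for a data analyst. The same section has an independent person carry out the randomization.

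Strengths and Limitations admits the lack of blinding and answers it this way: "to avoid researcher-induced bias, randomization and interviews will be conducted independently". The quantitative comparison is not among the activities named.

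Data Analysis describes that comparison in one sentence: "Differences between the groups will be compared using appropriate inferential tests". The person who does it is not identified.

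The Intervention section shows who is on the team. One investigator, "who developed the OHP program", trained the facilitators. The facilitators also appear to belong to the team, since "Sessions will be audio-recorded to be checked by another member of the research team to confirm fidelity of program delivery". Data Management and Monitoring gives the research team access to data held under a study number. It does not say that arm labels are hidden.

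**The concern.** A talking-based programme cannot be disguised from the person receiving it or the person delivering it. Analysing questionnaire scores is a separate task, done from a data file, and nothing about the programme stops that file from carrying neutral arm codes. The protocol therefore states as impossible a protection that is available to it. This is more than a detail left out of a short article, because the wording as it stands rules out masking for anyone on the team.

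At stake are the judgements made between raw questionnaires and a reported difference: incomplete items, odd or late responses, which records count, and how a result is read. Someone who knows the arms and has an interest in the programme can lean one way on these without intending to. The results inform the secondary objective of preliminary efficacy and, under Future Directions, are to serve as pilot data for a full trial.

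**Working it through.** The protocol gives no figure on this point, so there is none to reproduce. The check sets the stated reason and the stated safeguards against each role.

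1. **Participants.** They know whether they receive sessions. The reason applies.
2. **Facilitators.** They deliver five weekly sessions and a booster. The reason applies.
3. **Person who randomizes.** Described as independent, and necessarily knows the allocation. This person can hold the arm key.
4. **End-of-trial interviewer.** Independent and not the facilitator (Qualitative Interviews). Only intervention participants are interviewed, so there is no allocation to hide.
5. **Person who cleans, scores and compares the questionnaires.** Works from a file of five scales (PHQ-9, GAD-7, GSE, EQ-5D-5L, FAS) at baseline, 3 and 6 months. Both arms complete the same forms. The reason does not apply, and neither safeguard in Strengths and Limitations covers this role.

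Role 5 is the gap: the blinding sentence includes it, the reason does not reach it, and the safeguards leave it out.

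Two details decide whether an A/B file would really mask the arms:

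- **Study numbers.** Facilitators and colleagues who check sessions may know which numbers received the programme, so the file needs new numbers.
- **One-arm-only records.** Session recordings, fidelity checklists, the Course Experience Questionnaire and the end-of-trial interviews exist only for the intervention arm. Any of them in the file would reveal the code.

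Masking also has a limit. For the usual two-sided tests, swapping the arm labels changes only the direction of the result:

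- t-test on final score or on change: t becomes −t, and the p-value depends on |t|.
- Mann-Whitney: U becomes n₁n₂ − U. With 30 per arm this is 30 × 30 − U = 900 − U, with the same two-sided p-value.
- ANCOVA: the arm coefficient changes sign, with the same standard error and p-value.

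An analyst who can see the A/B grouping can therefore still try several tests and keep the smallest p-value. Coding the arms hides which side is favoured. Only fixing the test before any between-group result is seen prevents selection by result. The two steps are needed together.

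**The case against.** The strongest reply is that the name of the analyst, the handling of masked data and the choice of test commonly sit in a full protocol or statistical analysis plan, which is not shown. This stands for the choice of test: the sentence in Data Analysis is no fault in itself, and a plan may already fix the method. It does not dispose of the blinding sentence, which states an impossibility for the whole team on a reason that covers only part of it.

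A reader might infer that visible arm labels double the false-positive rate. A simulation can seem to show this. With no true effect, 30 per arm, a normal outcome, an assumed baseline correlation of 0.3 to 0.7 and 4,000 trials per setting, keeping the best of four ordinary tests gives 9.5% to 10.9% for one scale at one time point. Each test alone gives about 5%. By the label-swap argument, those figures are the same for a masked analyst who sees the grouping. They measure choosing a test after seeing results, and adding the second follow-up would add multiplicity. They do not measure blinding.

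A reader might also infer that knowing the arm tilts the interview coding, or that the developer or facilitators do that coding. The documents do not support either. Only intervention participants have the end-of-trial interview, and no coder is named. Moreover, "codes will be checked by another member of the research team to ensure appropriate and consistent coding process", and disagreements are settled by consensus against transcripts and recordings.

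Finally, the primary objectives concern feasibility and acceptability, no decision to proceed is tied to a p-value, and the lack of blinding is openly listed as a limitation. All of this stands, and it limits the weight of the point.

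**Conclusion.** The point holds in a limited form. The blinding statement is broader than its own reason, and the listed safeguards leave the arm comparison uncovered on a team that includes the programme's developer. That the developer or a facilitator will run the comparison is possible, not stated.

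The impact is modest. It falls on the secondary, preliminary-efficacy scales and not on recruitment or retention. The documents give no basis for putting a number on the bias. The conclusion assumes that the blinding sentence means what it says for every team member and that no unseen document already provides for a masked analyst. If one does, only the wording needs correcting. Because the remedy is cheap, the change is worth making even at this size.

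**What to change.** - In Randomization, Allocation, and Blinding, limit the statement to participants and those who deliver the programme, and say that the arm comparison will be done masked.
- Have the independent person who randomizes release a re-numbered questionnaire file with arms coded A and B, without any data that exist in one arm only.
- Fix scoring, cleaning rules and the test or model before any between-group result is seen and before the code is broken. If an analysis plan already does this, refer to it.
- Have an existing team member who neither developed nor delivered the programme run the comparison.
- Extend the sentence on safeguards in Strengths and Limitations to the analysis.
- Optional and minor: have at least one interview coder who is independent of programme delivery.

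The cost is a protocol amendment, agreed by the Data Management Committee and notified to the ethics committees as the protocol already requires, plus one extra file-handling step. Stored data are open only to the research team, so the amendment should also say how the independent person gets the file to be coded. The developer and facilitators give up running the comparison. The documents do not give the size of the team, so it is an assumption that a suitable member is available. Sample, visits and treatment do not change.
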